## Discussion

Existing literature suggests that psychosocial functioning is associated with depression severity and with longitudinal treatment outcomes (2, 3). Mutual interaction between psychosocial domains (e.g., work productivity, socializing) in depressed persons may exacerbate, maintain, or lead to recurrent depression. As an example, poor cognitive functioning may lead to issues maintaining work, which will cause financial strain and lead to reduced social interactions and impaired affect. Given the importance of psychosocial functioning in depression recovery, the development of treatments designed to target psychosocial functioning is justified.

Current research by the [name] group suggests that cognitive, emotional, and social cognitive domains underpin psychosocial functioning (12, 16). The CERT-D will target these domains with repeated training sessions over an 8-week intervention period. Cognitive and cognitive–emotional treatment approaches for depression have received empirical support (2, 32, 35). Initial research suggests treating social cognition may also be beneficial (16, 79, 80); however, further evidence is needed to establish the efficacy of treating social cognitive functioning in depression. The CERT-D study addresses this gap in knowledge by evaluating a treatment approach integrating all three underlying domains of psychosocial functioning (i.e., cognition, emotion processing, and social cognition). Treatment benefits of the CERT-D are intended to transfer to occupational functioning, resilience, functional abilities, and cognitive performance. Reinforcing improved performance and positive interaction between these domains is expected to develop a framework which encourages and rewards reduction of depression symptoms.

The directionality of recovery in the CERT-D is divergent from traditional depression therapies. That is, existing therapies (e.g., psychotherapy) target reduction in negative depression symptoms with the expectation that improvements in functional and psychosocial domains will follow. By contrast, the current treatment targets psychosocial and functional improvements from the outset. Importantly, the CERT-D integrates treatment across cognitive, emotional, and social domains rather than focusing on one of these domains alone. Integrating treatment across multiple domains is intended to counteract negative feedback between impaired domains which may occur in more selective treatments.

A possible disadvantage of administering training across three domains is that treatment benefits to cold cognitive functioning (e.g., executive functioning) will be attenuated in comparison to traditional cognitive remediation. Reduced executive gains in the CERT-D treatment could result from the equal emphasis given to social, emotional, and cognitive domains, as opposed to focusing purely on cold cognition. However, we do not anticipate this issue to be a crucial issue for two key reasons: (1) emotional and social–cognitive training demand similar cognitive effort and are equally complex in comparison to traditional cognitive training. As a result, emotional and social training may also benefit executive functioning. (2) Individuals who demonstrate significantly impaired cold cognition will be allocated to the “High Cognition” program within the personalized arm. This treatment program emphasizes cognitive treatment above emotional and social domains, and will hence evaluate the efficacy of predominantly cognitive training, relative to training all three domains in the “standard” treatment group. If cognition training alone is identified as having greater clinical efficacy than the integrated training approach, then this finding will also contribute to the value of the current study.

In summary, the CERT-D will make three primary contributions: (1) the evaluation of a novel psychological treatment for depression. Psychosocial function is considered the primary outcome, and is expected to be improved by integrated treatment of underlying domains. (2) The comparison of the relative clinical efficacy of personalized and standard treatment approaches. Taking baseline deficits into account may enable more efficient and effective psychosocial recovery, as impaired domains receive greater attention. In combination, contributions (1) and (2) may lead to the development of an intervention which could be conducted in parallel or in lieu of other treatments for depression. (3) The current study will also improve our understanding of the genomic, neurological and biological correlates of psychosocial and cognitive dysfunction in depression. Taken together, these findings will advance the field of personalized psychiatry by evaluating the relative efficacy of a standard and personalized treatment approach, in addition to testing the overall value of targeting psychosocial deficits in MDD.

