### Study Design and Recruitment

The CERT-D study will commence in July 2017. The study will be a RCT, comparing the clinical efficacy of a personalized and standard intervention. Psychosocial functioning is considered the primary outcome. An effect size of approximately *d* = 0.5 is expected with regards to change in psychosocial function over the intervention. Given the intended sample size of 100, the study will achieve statistical power of 89% (1 − β = 89). The rationale for this “medium” effect size is that previous interventions have found positive outcomes approximate to this magnitude (5, 35), for example in cognitive functioning.

The trial will include 16 treatment sessions designed to improve cognition, emotion processing, and social cognition administered over an 8-week period. Assessments will occur at baseline, 4 weeks (mid-RCT), 8 weeks (end of RCT), and in the observational period at baseline (week 9) and 3 and 6 months post-RCT (see Figure 1). Assessments will measure psychosocial functioning, cognition, emotional state, social cognition, as well as occupational functioning, depression symptom severity, functional disability, cognitive failures, and resilience. Three assessment visits will also include taking blood for biomarker and genetic analysis. Recruitment will include individuals between the ages of 18 and 75, who will be invited to participate *via* research clinics of the Department of Psychiatry, University of Adelaide, and within the Central Health Network in Adelaide, South Australia. It could be argued that the age range should be restricted to younger adults (<60), such that subjects with geriatric depression are excluded. However, recent work has suggested that cognitive training strategies are efficacious in the treatment of geriatric depression (47, 51, 52). Given the current intervention shares many components of traditional cognitive training, it is suggested that the CERT-D intervention should benefit older (i.e., 60–75 years) patients.

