### Randomization Process

After screening, subjects will be randomly allocated with computer software to receive either personalized or standard (non-personalized) treatment (see Figure 2). In both the standard and personalized intervention groups each treatment session will consist of domain-specific tasks. Every treatment session will be repeated at least once, to ensure that subjects have the opportunity to practice the treatment tasks.

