### Personalized Treatment

Personalized interventions will be tailored to address subjects’ most impaired domains. Domain-specific tests will be administered at baseline to determine the modality and degree of individual impairment. On the basis of baseline deficits, subjects in the personalized group will be allocated to one of four potential treatment arms; (1) high cognition treatment, (2) high emotion treatment, (3) high social cognition treatment, and (4) broad impairment treatment (see Figure 2). Subjects will be allocated to streams 1, 2, or 3 if impairment is primarily represented in one of the three baseline domains. In treatment arms, 1–3 subjects will complete a greater number of intervention sessions devoted to the domain of primary dysfunction. Subjects who are significantly impaired in two or more domains will be allocated to broad impairment treatment. Broad impairment treatments will incorporate a similar number of intervention sessions in each domain, but will be initiated more gradually (i.e., initial treatment sessions will be shorter in duration) and will use simpler tasks.

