### Standard Treatment

Subjects allocated to the standard (i.e., non-personalized) intervention will receive an identical intervention regardless of baseline impairment. The standard intervention will be comprised of approximately an equal number of treatment sessions in each domain. Unlike broad impairment treatment, standard treatment sessions will be the full duration from the outset and the difficulty curve of treatment tasks will be steeper.

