## Intervention Outcomes, Analyses, and Dissemination

The primary outcome of the CERT-D will be psychosocial functioning. Specifically, it is expected that psychosocial functioning will improve at 8 weeks (end of RCT) relative to baseline. Post-RCT psychosocial functioning is expected to be maintained over the 6 months observational period. Performance in secondary outcome measures is expected to demonstrate a similar effect of treatment. Secondary outcomes include depression symptom severity, occupational functioning, resilience, functional disability, and perceived cognitive failures. In addition, the personalized treatment group is expected to show greater improvement over time relative to the standard treatment group. Finally, the association between biomarkers and psychosocial and cognitive performance before and following treatment will be evaluated.

Statistical analyses will be performed with a mixed model ANOVA with time (baseline, 8 weeks, baseline post-RCT, 3 months post-RCT, 6 months post-RCT) and treatment type (personalized, standard) as independent variables. Psychosocial functioning (FAST score) will be the dependent variable. It is expected that overall psychosocial functioning will improve at post-treatment relative to baseline, and that this improvement will be greater in the personalized treatment arm relative to the standard treatment arm. Biomarker analyses require specifically tailored software and will ultimately be entered into simple and stepwise linear regression analyses. These analyses will determine whether individual biomarkers (e.g., CRP), or combinations of biomarkers, are related to cognition (i.e., THINC-it performance) or psychosocial functioning.

Within the personalized treatment group, further analyses will evaluate whether there are any differences in psychosocial functioning owing to the domain-specific treatment groups. That is, will there be any differences in post-RCT psychosocial functioning between the high cognition, high emotion, and high social cognition treatment groups? Given the novelty of the current treatments, these analyses will be exploratory. As with the primary outcome, analyses for this outcome will be conducted with mixed model ANOVAs.

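### Both planned stream comparisons confound the patient's baseline deficit with the training received; compare the arms within the same deficit class instead

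*Protocol article*

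**What the plan says.** Under Randomization Process, the only random step is between the two arms: "After screening, subjects will be randomly allocated with computer software to receive either personalized or standard (non-personalized) treatment". Under Personalized Treatment, streams are a matter of patient type: "On the basis of baseline deficits, subjects in the personalized group will be allocated to one of four potential treatment arms". Under Standard Treatment, everyone in the other arm gets the same programme whatever their deficits, and no classification of that arm is described.

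Two comparisons are then built on the streams.

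- **High Cognition stream against the standard arm.** The Discussion answers a worry about reduced executive gains by saying that this programme "will hence evaluate the efficacy of predominantly cognitive training, relative to training all three domains in the" standard group. No caveat follows. It goes on to speak of cognition training on its own being found superior to the integrated approach.
- **Stream against stream.** The section Intervention Outcomes, Analyses, and Dissemination asks: "will there be any differences in post-RCT psychosocial functioning between the high cognition, high emotion, and high social cognition treatment groups". Mixed model ANOVAs are planned. The analyses are called exploratory, and the reason given is that the treatments are new.

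**The concern.** A participant is in the High Cognition stream because cognition was the dominant deficit. The standard arm contains all deficit patterns. A difference between the two may come from the training or from the kind of patient, and the data as described cannot tell these apart. The stream-versus-stream comparison has the same problem in a purer form: deficit determines stream, so each training is seen in only one kind of patient.

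The article's own model makes this more than a formality. It holds that cognition, emotion processing and social cognition underlie psychosocial functioning, which is the primary outcome. On that model the deficit groups may well differ on the Functioning Assessment Short Test (FAST) even under identical training.

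At stake is a conclusion about which training works, in a trial meant to inform personalized psychiatry, that could rest on differences between patients.

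**Working it through.** **1. What the plan's power figure covers.** Study Design and Recruitment gives an effect of d = "0.5 is expected with regards to change in psychosocial function over the intervention" and says: "Given the intended sample size of 100, the study will achieve statistical power of 89" per cent. One reading reproduces this: a between-groups repeated-measures F test with f = 0.5/2 = 0.25, N = 100, 5 measurements, and (my assumptions) 1:1 allocation, correlation 0.5 and two-sided 5%.

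λ = N f² m / (1 + (m − 1)ρ) = 100 × 0.0625 × 5 / (1 + 4 × 0.5) = 10.4 on 1 and 98 df, power 89.2%.

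A plain two-sample t test at 50 per arm gives 69.7%. In the matching reading, 89% refers to the two randomized groups. Nothing is stated for any stream comparison.

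**2. What each comparison holds fixed.**

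| Comparison | Deficit type equal? | Randomized? |
|---|---|---|
| Personalized vs standard, all participants | yes, in expectation | yes |
| High Cognition stream vs whole standard arm | no | no |
| Stream vs stream, personalized arm | no, differs by definition | no |
| Personalized vs standard, same deficit class | yes, in expectation | yes, within class |

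**3. The sign depends on the contrast.** Assume a stream starts 0.4 SD worse on FAST than its comparator, correlation 0.5, and no treatment difference.

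- Post scores: 0.4 × 0.5 = 0.2 SD worse, a spurious deficit.
- Change from baseline: 0.4 − 0.2 = 0.2 SD more improvement, a spurious gain.
- Baseline-adjusted: 0.2 − 0.5 × 0.4 = 0, but only because this example sends the whole prognostic difference through baseline FAST. Any further effect of the deficit on later FAST would remain.

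**4. Size against the whole standard arm.** Suppose the High Cognition class differs from the other classes by δ SD in outcome and makes up a share q of each arm of 50. The standard arm contains the same share of such patients, so bias = δ(1 − q). With n in the stream, SE = √(1/n + 1/50), and the rejection rate under no treatment difference is Φ(−1.96 − bias/SE) + 1 − Φ(1.96 − bias/SE). The last two columns are for a two-sample t test with n per arm within the class.

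| q (n) | Bias; rejection, δ = 0.2 | Bias; rejection, δ = 0.5 | Within-class power, d = 0.5 | Detectable d at 80% power |
|---|---|---|---|---|
| 15% (8) | 0.17; 7.3% | 0.425; 20.0% | 15.4% | 1.51 |
| 25% (12) | 0.15; 7.5% | 0.375; 21.5% | 21.6% | 1.20 |
| 33% (16) | 0.134; 7.5% | 0.335; 21.5% | 27.8% | 1.02 |
| 40% (20) | 0.12; 7.4% | 0.30; 20.5% | 33.8% | 0.91 |

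**5. Check by simulation.** Over 4,000 runs (q = 25%, δ = 0.5, no treatment effect), the stream against the whole standard arm gave a mean difference of 0.37 SD and 19% rejection. The same deficit class compared across arms gave −0.006 SD and 5.4%.

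**6. Training content.** The Personalization part of the Introduction and the Personalized Treatment section describe the dominant domain as getting more sessions and the others fewer. No stream delivers cognition training by itself, so the Discussion's remark about it has no matching group.

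**The case against.** The best defence has four parts. The stream-versus-stream comparison is put as a question and labelled exploratory. The High Cognition comparison appears in the Discussion, and the analysis section specifies no test for it. The planned mixed model includes baseline as a time level. The prognostic differences used above are assumed.

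Of this, the last part stands: the article supports no single size, only a range. The others do not remove the problem. The exploratory label rests on novelty and says nothing of non-random assignment. The Discussion states its inference outright. Including baseline changes the sign of the bias in the example and does not make the groups alike.

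Three stronger readings are tempting, and the article does not support them.

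- **That both arms must be classified before randomization, with stratification.** A reader might infer this, but one rule applied to pre-treatment data in both arms is enough, even at analysis, provided that allocation did not influence baseline testing. The assessment sections describe the baseline battery for participants in general.
- **That classifying the standard arm would make the streams comparable with each other.** It would not. Within the personalized arm, deficit still determines stream. Classification only permits arm comparisons within a class.
- **That the main comparison is damaged because the broad stream resembles standard treatment.** The domain mix is indeed similar: "Broad impairment treatments will incorporate a similar number of intervention sessions in each domain", and "The standard intervention will be comprised of approximately an equal number of treatment sessions in each domain". But the two differ in early session length and in difficulty, and Hypothesis 3 tests personalization as a whole policy, of which the broad stream is part. An effect in single-domain participants only is a different estimand, and any dilution figure needs a broad share and a zero benefit that the article does not give.

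**Conclusion.** The concern holds for the two stream comparisons and no further. As described, neither can separate the effect of training from the prognosis of the deficit, and the Discussion's claim about predominantly cognitive training is not supported by the design.

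Against the whole standard arm, the spurious difference is about 0.12 to 0.17 SD if the deficit class differs by 0.2 SD, and 0.30 to 0.43 SD if it differs by 0.5 SD. The upper end is not far below the d of 0.5 that the trial expects. These figures rest on assumed stream shares of 15 to 40%, 50 per arm and no true treatment difference. The direction cannot be stated in advance, because post scores and change scores can point opposite ways.

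The randomized personalized-versus-standard comparison remains unbiased by this point.

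**What to change.** 1. Write down one stream rule and apply it to pre-treatment baseline data in both arms, scored without regard to allocation, and before allocation if feasible. Personalized Treatment sends participants impaired in two or more domains to the broad stream, while the Discussion sends those with significantly impaired cold cognition to High Cognition. These passages must be reconciled so that a single rule exists.
2. Replace the High Cognition versus whole-standard comparison with personalized versus standard within the same deficit class: an arm-by-class term, adjusted for baseline FAST, declared exploratory.
3. Label any stream-versus-stream result as non-randomized and descriptive.
4. Withdraw the Discussion's statements that the trial evaluates predominantly cognitive training, or cognition training by itself, against integrated training.

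The cost is scoring the standard arm from the baseline battery, plus wording. The drawback is precision: four equal classes leave about 12 per arm per class (50/4 = 12.5), with power of about 22% at d = 0.5 and a detectable effect of about d = 1.2 at 80% power. Within-class results should be given as estimates with intervals and not as tests of efficacy.

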Social cognition is typically evaluated by one’s ability to read facial emotions (42). Depressed persons are typically impaired in facial affect recognition, in part due to a tendency to negatively interpret facial emotions (43). A plausible explanation is that impaired attention and emotional interpretation may cause depressed individuals to focus on mood-congruent (i.e., negative) features of facial affect. Other studies of social cognition employ videos of social interactions, which are intended to be more naturalistic and contain more dynamic social features (i.e., body language, prosody, verbal information) (44, 45). These tasks emphasize theory of mind, as reliance on syntactic and visual information alone is insufficient to detect nuanced social interactions (e.g., sarcasm). Social cognition can also be measured with prosody tasks, in which several syntactically identical sentences are presented with different emotional intonations.

The current treatment will use an integrated approach in which cognitive remediation and cognitive training techniques are employed with cognitive, emotional, and social cognitive stimuli. While traditional cognitive training has been shown to increase psychosocial functioning (46, 47), it is expected that the addition of emotional and social training domains will extend and enhance this effect. Similar techniques have been employed to address emotional and social impairment in other psychiatric illnesses, including bipolar (48) and schizophrenia (49). The results of these studies suggest that social and emotional training may provide benefits in domains of daily life (e.g., occupational functioning). The clinical efficacy of these strategies in treating major depression has not yet been evaluated and is hence a primary interest of the current study. It is expected conducting remediation and training in three domains (i.e., cognition, emotion processing, and social cognition) will improve psychosocial functioning to greater extent than is achieved by treating cognition alone.

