### Personalization

Given the multifaceted nature of impairment in depression, it is reasonable to assume that deficits will not occur in a uniform nature within individuals. Certain individuals may be disadvantaged specifically in domains of emotional processing, while others are more disadvantaged in terms of cold cognitive ability or social cognition. Previous interventions may not have led to consistent improvements in psychosocial functioning because individual differences in domain-specific impairment were not addressed. In fact, existing interventions assume that group means (i.e., norms) reflect impairment at an individual level, and hence that a generalized treatment approach is sufficient. Given the heterogeneity of impairment observed between individuals with MDD (12), it is possible that a standard treatment approach is not optimal (50). In particular, standard treatment approaches may misappropriate resources and time to clinical domains which are not relevant or helpful to the individual. In contrast, personalized approaches tailor treatment by targeting baseline deficits within individuals, enabling treatment to focus on impaired domains, while also spending less time addressing more functional domains. Personalization may improve treatment efficiency and efficacy, in contrast to the traditional standard approach.

The current investigation will evaluate the personalized approach, by comparing psychosocial functioning following a personalized intervention and a standard (i.e., non-personalized) intervention. The personalized intervention will tailor treatment tasks around baseline individual deficits, such that the individual’s most impaired domains receive the greatest attention. Given the importance of cognition, emotion processing, and social cognition in determining psychosocial functioning, the CERT-D treatment will be tailored by patterns of impairment observed in these three domains. For example, a participant who demonstrates severe cognitive impairment will receive a greater number of treatment sessions devoted to cognition, with fewer sessions devoted to emotion processing and social cognition. Overall, it expected that both personalized and standard treatments will result in improved psychosocial functioning, which is expected to be retained over a 6-month observational period. However, it is predicted that the clinical effect on psychosocial function will be greater following personalized, relative to standard, treatment.

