In summary, the cognitive and emotional recovery training program for depression (CERT-D) study will evaluate a novel treatment for depression, employing an integrated cognitive, emotional and social cognitive approach. The primary outcome will be change in psychosocial function over the intervention and subsequent observational period. Performance in several secondary domains will also be evaluated, including depression symptom severity, resilience, occupational functioning, cognitive failures, and functional disability. In addition, the study will examine biomarkers of cognitive and psychosocial dysfunction in depression, providing an opportunity to expand our knowledge of this domain. This research will advance the field by evaluating the efficacy of integrating training of cold cognition with emotion processing and social cognition. The integrated approach contrasts with traditional cognitive remediation, which has primarily focused on the improvement and application of executive training. In addition, the current methods allow evaluation of the relative clinical efficacy of personalized and standard treatment approaches in remediating psychosocial dysfunction in MDD.

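### The article treats a comparison with cognition training alone as something the trial could inform, but no arm or stream receives cognition training alone, so the added value of emotion and social cognition training cannot be estimated

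*Protocol article*

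**What the plan says.** Two places in the protocol article refer to cognition training on its own. In the Introduction, under Social Cognition, the expectation is that training in three domains "will improve psychosocial functioning to greater extent than is achieved by treating cognition alone". In the Discussion, the paragraph on possible disadvantages answers the worry that gains in cold cognition may be diluted. It points to the High Cognition stream as a test of mainly cognitive training against the standard group, and continues: "If cognition training alone is identified as having greater clinical efficacy than the integrated training approach, then this finding will also contribute to the value".

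The design sections describe something different:

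- **Randomization Process:** "subjects will be randomly allocated with computer software to receive either personalized or standard (non-personalized) treatment". There are two randomised arms and no third.
- **Standard Treatment:** sessions are divided about equally among cognition, emotion processing and social cognition.
- **Personalization:** the example participant with severe cognitive impairment "will receive a greater number of treatment sessions devoted to cognition, with fewer sessions devoted to emotion processing and social cognition".
- **Discussion, on the High Cognition stream:** "This treatment program emphasizes cognitive treatment above emotional and social domains".
- **Personalized Treatment:** participants in the personalized arm are placed in one of four streams according to their baseline deficits.

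**The concern.** Within two sentences the Discussion moves from mainly cognitive training to cognition training alone, as if the first could stand in for the second. Everyone in this trial receives some form of the integrated programme, and only the proportions differ. A difference between High Cognition and standard treatment would concern a heavier versus an even cognitive share. It would not show whether the two newer domains add anything to cognition training.

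Integration across domains is what the article presents as new, and the Discussion uses the High Cognition stream as one of two reasons to set aside the dilution worry. A later reader could take a stream result as evidence about adding emotion and social cognition training, which the trial does not supply.

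There is a second problem with the contrast the Discussion names. High Cognition participants are selected for impaired cognition, whereas the standard arm takes everyone randomised to it. The comparison therefore mixes the effect of session share with the effect of baseline profile.

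**Working it through.** **Step 1. Is there a cognition-only group?** Set the planned treatments against the condition named in the Introduction and Discussion.

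| Group | Content as described | Cognition only? |
|---|---|---|
| Standard arm | three domains, about equal | no |
| High Cognition stream | more cognition, fewer of the other two | no |
| High Emotion and High Social Cognition streams | more sessions in the named domain | no |
| Broad impairment stream | similar number in each domain, gentler start | no |

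Participants planned for cognition training alone: 0 of 100. A contrast with an empty group has no estimate and no power, whatever the analysis method.

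**Step 2. How far apart are the groups that do exist?** There are 16 sessions. Standard arm: 16 / 3 = 5.3 cognition sessions, about 33%. The article gives no session count for High Cognition. If it were 8 to 10 (an assumption), the share would be 8/16 = 50% to 10/16 = 63%. The available contrast would then be 50–63% against 33%, whereas the claim needs 100% against 33%. Step 1 does not depend on this assumption.

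**Step 3. Is the comparison planned?** The Objectives list four hypotheses: change over time, secondary outcomes, personalized versus standard, and biological signatures. The analysis section adds exploratory comparisons among streams inside the personalized group. Neither contains a contrast with cognition alone, nor High Cognition versus standard.

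**Step 4. How informative would the nearest contrast be?** The plan gives no figure for it. Its one power figure (89% for d = 0.5, N = 100) concerns change over the intervention and plays no part here. It cannot be checked from the stated inputs alone, since alpha, sidedness and within-person correlation are not given. At two-sided alpha 0.05, 50 versus 50 gives 70.5% and a paired test on 100 gives 99.9%. A repeated-measures between-group test with five time points and an assumed correlation of 0.5 gives 89.2%.

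For illustration, assume equal allocation (50 per arm), two-sided alpha 0.05, and borrow d = 0.5. Then power ≈ Φ(d / √(1/n₁ + 1/n₂) − 1.96).

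- *Stream against the whole standard arm (not randomised).* With n₁ = 10, n₂ = 50: 0.5 / √0.12 = 1.443, and Φ(−0.517) = 30%. With n₁ = 20: 0.5 / √0.07 = 1.890, and Φ(−0.070) = 47%.
- *Stream against standard-arm participants with the same deficit.* Under equal allocation about as many are expected as in the stream. With 5 versus 5, 12%. With 10 versus 10: 0.5 / √0.2 = 1.118, and Φ(−0.842) = 20%. With 15 versus 15, 28%.

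Stream sizes are assumed, as the article gives none.

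**The case against.** The strongest defence is that nothing formal rests on these sentences. The Discussion sentence is conditional and the Introduction sentence is an expectation. The comparison is absent from the objective, the hypotheses, the planned analyses and the three closing contributions. The sentence just before the quoted one describes the stream accurately as mainly cognitive, so the later phrase may be loose shorthand.

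Most of this stands, and it limits the point. A reader might infer that the protocol undertakes to show whether three-domain training beats cognition alone. It does not: it expects this in one place and implies in another that the reverse could be found. Nor does the Discussion speak of cognition alone proving worse; it mentions only greater efficacy.

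A reader might also count the summary under Personalization as an error: "This research will advance the field by evaluating the efficacy of integrating training of cold cognition with emotion processing and social cognition". That can fairly be read as evaluating the integrated programme as a whole. It names no cognition-only comparator and needs no change.

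The shorthand defence does not remove the problem. Even read as shorthand for the High Cognition stream, the sentence sets that stream against the integrated approach, although the stream is itself integrated training with different weights. The Introduction sentence has no such nearby qualification.

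**Conclusion.** The point holds as a misstatement of what the design can show. No arm or stream is cognition-only (0 of 100 by design), so the trial can neither support nor refute the expected superiority over cognition alone. It also cannot identify cognition training alone as more effective. This follows from the article's own description and needs no numerical assumption.

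The contrast the Discussion does name addresses a weaker question, a heavier versus an even cognitive share. Against the whole standard arm it is confounded with baseline impairment. Against like participants it would have roughly 12% to 28% power at d = 0.5 for 5 to 15 per group, where the stream sizes, equal allocation and alpha are assumptions.

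It would be wrong to infer that the trial's main results are compromised. The randomised personalized versus standard comparison and the planned FAST analysis do not use this contrast and are unaffected.

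**What to change.** 1. In the Discussion, replace the reference to cognition training alone with *cognition-weighted training*, compared with evenly divided training.
2. In the Introduction, under Social Cognition, keep the expectation if wished, but add that superiority over cognition alone is not tested in this trial.
3. State that any High Cognition versus standard result is exploratory and that the stream is not formed by randomisation. Make the comparison only against standard-arm participants who meet the same baseline-deficit rule, applied identically in both arms. The cognition, emotion and social cognition assessments already collected at baseline should allow this, assuming the stream rule can be computed from them.

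The cost is almost wholly wording, with no new visits or measurements. The sponsor gives up a claim the design cannot support and accepts that the restricted comparison will be small and imprecise.
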